# Efficacy and safety of cytokines versus first-line sunitinib and second-line axitinib for patients with metastatic renal cell carcinoma (ESCAPE study): A study protocol for phase III randomized sequential open-label study

**DOI:** 10.1016/j.conctc.2019.100403

**Published:** 2019-06-26

**Keywords:** Cytokine, Interferon alfa, Interleukin-2, Sunitinib, Axitinib, Metastatic renal cell carcinoma

## Abstract

Appropriate protocol for the sequential treatment of metastatic renal cell carcinoma (mRCC) has not been established yet. Some mRCC cases with favorable risk were reported to achieve complete remission and durable response using interferon alfa (IFNα) + low dose interleukin-2 (IL-2). Cytokine therapies may be suitable for some patients with mRCC as first-line therapy. The present study is a phase III, investigator-initiated, multicenter, prospective randomized controlled trial investigating patients with low and intermediate risk mRCC classified by Memorial Sloan-Kettering Cancer Center risk criteria to evaluate the efficacy and safety of sequential treatment with cytokine (IFNα + IL-2) as first-line and axitinib as second-line therapy versus sequential treatment with sunitinib as first-line and axitinib as second-line therapy, which is the current standard treatment for patients with favorable risk. The target sample size was set at 72 patients per group (total 144 cases). The study duration is 7 years, and the duration for recruitment is 4 years. Our expectation of this trial is to clarify first- and second-line sequential treatment for mRCC better, especially in patients with favorable risk and some with intermediate risk. The results of this trial will certainly contribute to new information for the strategy of first- and second-line sequential treatment for mRCC.

**Trial registration:**

University hospital Medical Information Network (UMIN) Center identifier UMIN 000012522.

## Introduction

1

Recently developed molecular target drugs and immune checkpoint inhibitors have changed treatment strategies for metastatic renal cell carcinoma (mRCC) because of their efficacy; however, complete recovery from mRCC remains very rare [[1], [2], [3]]. Therefore, our current realistic goal for mRCC treatment would be maximum elongation of overall survival (OS) of patients while maintaining their quality of life (QOL). To achieve the goal, we must plan longitudinal treatment strategies that consider the general condition of the patient and control adverse events (AEs) of administered drugs. However, an appropriate protocol for sequential treatment of mRCC has yet to be established. The number of patients who can undergo treatment is gradually decreasing, as the treatment lines are increasing to second-, third-, and fourth-line, because the general condition of patients worsens with disease progression and/or AEs of the drugs. To extend OS of patients with mRCC as long as possible, selecting the first-line and consecutive second-line therapy is extremely important. Based on the guidelines for mRCC treatment and the current Japanese system of national insurance, the recommended drug selection for mRCC categorized as favorable risk by the Memorial Sloan-Kettering Cancer Center (MSKCC) criteria [4,5] is sunitinib [1] or pazopanib [3] as first-line drug, and axitinib [2] or nivolumab [6] as second-line. However, OS in patients treated with cytokines, which have been used for a long time for mRCC in Japan, has been reported to be better than in western countries [7]. Therefore, it is speculated that the effectiveness of cytokines is better for Japanese patients than for western patients. Some mRCC cases meeting favorable risk criteria were reported to have achieved complete remission (CR) and durable response using interferon alfa (IFNα) + low dose interleukin-2 (IL-2) [8,9]; however, molecular targeted treatments may not achieve CR for patients with mRCC. Cytokine therapies are not effective in patients with high risk mRCC, but cytokine therapy may be effective for some patients with intermediate risk mRCC, because patients with intermediate risk mRCC are part of a heterogenous group [10].

We planned a prospective randomized controlled trial (RCT) for patients with low and intermediate risk mRCC (classified by MSKCC risk criteria) to evaluate the efficacy and safety of sequential treatment of cytokine (IFNα + IL-2) as first-line and axitinib as second-line therapy versus sequential treatment of sunitinib as first-line and axitinib as second-line therapy, which is the current standard treatment for favorable risk mRCC (ESCAPE Study).

## Material and methods

2

### Aim of the study

2.1

To assess the efficacy and safety of cytokines versus sunitinib as first-line therapy followed by axitinib as second-line therapy in the treatment of patients with mRCC.

### Study design

2.2

The present study is a phase III, investigator-initiated, multicenter RCT involving a head-to-head comparison of IL-2 plus IFNα vs. sunitinib as first-line therapy followed by axitinib as second-line therapy for patients with mRCC. Patients will be randomly assigned to IL-2 plus IFNα or sunitinib-axitinib treatment group, as shown in Fig. 1.

**Fig. 1 fig1:**
[figure not shown]
Trial registration: UMIN000012522.

### Additional measures

2.3

A validated health-related QOL (HRQOL) questionnaire, the European Organization for Research and Treatment of Cancer (EORTC) QLQ-C30, the Functional Assessment Of Cancer Therapy-Kidney Symptom Index-Disease Related Symptoms (FKSI-DRS), and the EuroQol Group (EQ)-5D that has been translated into Japanese will be administered before treatment, at 2 and 4 months after the beginning of first-line treatment, and at the time of completion or drop out of second-line treatment to comprehensively evaluate the various aspects of physical and psychosocial well-being.

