### Administration of IFNα plus IL-2 vs. first-line therapy with sunitinib followed by second-line with axitinib

2.8

Patients assigned to cytokine group receive intravenous injection of IL-2 at a dose of 700,000 unit/day five days/week for the initial 2 or 4 weeks, and then, one or three times/week as maintenance plus subcutaneous injection of IFNα 5–6 million units two or three times/week (Fig. 2). Sunitinib at a dose of 50 mg/day is orally administered to patients who are assigned to the sunitinib group, and one course consists of 4 weeks of administration and 2 weeks of withdrawal. A schedule of 2 weeks of administration and one week of withdrawal is also permitted. Reduction of doses is permitted if a clinical investigator considers the basic doses inappropriate for any reason. The administration of IL-2 plus IFNα or sunitinib is terminated when progressive disease (PD) is confirmed based on RECIST v.1.1, the patient dies, or severe AEs occur. A clinical investigator administers axitinib as second-line treatment immediately after confirmed comprehensive evaluation of PD based on RECIST v.1.1 during first-line treatment. In case of cessation of first-line treatment because of severe AEs, a clinical investigator may consider restarting first-line treatment after recovery below grade 2. Axitinib at a dose of 10 mg/day (5 mg dose twice per day) is orally administered to patients as second-line treatment. Dose reduction or dose increase up to 20 mg/day (10 mg dose twice per day) is permitted if a clinical investigator considers the basic doses inappropriate for any reason. The administration of axitinib is terminated when PD is confirmed by comprehensive evaluation based on RECIST v.1.1, the patient dies, or severe AEs corresponding to discontinuation criteria occur. Zoledronic acid and denosumab are permitted for patients with bone metastasis.

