### Data collection

2.9

All the patients provide written informed consent to participate in the study and are asked to complete a medical history. Clinical data obtained in the ESCAPE study include the ECOG performance status, physical examination findings (e.g., height, body weight, body temperature, and blood pressure), results of hematologic examination (e.g., red blood cell count, hemoglobin, hematocrit, platelet count, white blood cell count, and differential count of leucocytes), results of blood biochemical examination (e.g., liver enzymes, alkaline phosphatase, total bilirubin, total protein, albumin, creatinine, lipids, fasting blood sugar, hemoglobin A1c, C-reactive protein, and electrolytes), results of urinalysis, chest X-ray imaging, lung to pelvic CT or MRI, brain CT or MRI, bone scintigraphy, electrocardiography, and the questionnaires for HRQOL (e.g., EORTC QLQ-C30, FKSI-DRS, EQ-5D). The X-ray, brain CT, and bone scintigraphy are performed at the time of study registration. Other examinations are performed every 2 months from the date of the commencement of treatment to month 24 and every 3 months after month 24 until the study is completed (Fig. 3). However, examinations can be performed at any time, if the clinical investigator considers them to be necessary.

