### Seven secondary endpoints are set in the ESCAPE study

2.11

1.OS, defined as the time from randomization to death from any cause.2.Each PFS in first-line treatment and second-line treatment based on RECIST v.1.1 criteria.3.Objective response rate (ORR), defined as the proportion of CR and partial response (PR) cases in total cases based on best overall response using RECIST v.1.1 criteria, and disease control rate (DCR), defined as the proportion of CR, PR, and stable disease (SD) cases in total cases in first-line and second-line treatment.4.Time to treatment failure (TTF), defined as the time from commencement of first-line therapy to earliest time of PD using RECIST v.1.1 criteria, death from any cause, or cancellation of therapy in first-line treatment.5.Total TTF from first-line to second-line treatment, defined as the time from commencement of first-line therapy to earliest time of PD using RECIST v.1.1 criteria, death from any cause, or cancellation of the therapy in second-line treatment.6.Safety in first-line and second-line treatment evaluated by Common Terminology Criteria for Adverse Events v4.0 system.7.HRQOL in first-line and second-line treatment evaluated by EORTC QTQ-C30, FKSI-DRS, and EQ-5D.

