### Planned statistical analyses

2.14

Intention-to-treat analyses in each group will be performed, and survival curves will be estimated with Kaplan-Meier method. A log-rank test will be used to evaluate differences in the survival curves between the two groups of patients. Hazard ratio will be estimated with the Cox proportional hazard model. Restricted mean survival time will be considered to quantify the treatment benefit in the absence of proportional hazard assumption in survival curves. ORR (CR + PR) and DCR (CR + PR + SD) in each group using the best response evaluated by RECIST v1.1 will be estimated for 95% confidence interval with Clopper-Pearson method. AEs in each group will be aggregated by grades and types, and the proportion of AEs will be compared between the groups by Fisher's exact test. The chronological changes in the HRQOL from the baseline evaluation using EORTC QLQ-C30, FKSI-DRS, and EQ-5D will be compared. All the tests will be two-sided, and a *P*-value of 0.05 will be considered statistically significant.

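### Sections 2.3 and 2.9 give inconsistent HRQOL schedules; if 2.3 governs, second-line HRQOL rests mainly on one event-triggered form with no value at the start of axitinib

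*Protocol article*

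**What the plan says.** All references are to the protocol article.

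- **Section 2.3 (Additional measures)** gives EORTC QLQ-C30, FKSI-DRS and EQ-5D before treatment and then "at 2 and 4 months after the beginning of first-line treatment, and at the time of completion or drop out of second-line treatment". That makes four times in all.
- **Section 2.9 (Data collection)** ends its list of study data with "electrocardiography, and the questionnaires for HRQOL (e.g., EORTC QLQ-C30, FKSI-DRS, EQ-5D". It then separates the baseline-only items: "The X-ray, brain CT, and bone scintigraphy are performed at the time of study registration". Everything else follows the next sentence: "Other examinations are performed every 2 months from the date of the commencement of treatment to month 24", with 3-monthly examinations after that until the study ends. The questionnaires are not among the baseline-only items.
- **Section 2.11, secondary endpoint 7**, is "HRQOL in first-line and second-line treatment evaluated by" the three instruments. Second-line is therefore explicitly part of the endpoint.
- **Section 2.14 (Planned statistical analyses)** says of the analysis: "The chronological changes in the HRQOL from the baseline evaluation" will be compared.
- **Section 2.8** starts axitinib directly after confirmed first-line progression. It stops axitinib at progression, death or severe adverse events.

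**The concern.** A site following 2.3 and a site following 2.9 would collect very different HRQOL data. Under 2.3 nothing is collected at the switch to axitinib, and nothing is scheduled while the patient takes it. The only form tied to second-line comes when that line ends, usually because of progression or toxicity. It records the patient's state at failure rather than quality of life on treatment, and it has no second-line starting value to be compared with.

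The Introduction sets the aim as longer survival with quality of life preserved, and the trial compares whole sequences. If the sequences differ in how patients feel on axitinib, the 2.3 schedule would largely miss it. This cannot be left to an analysis plan, because no analysis recovers forms that were never collected.

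**Working it through.** **Inputs.** Planning durations from section 2.13: 10.4 + 15.7 = 26.1 months (cytokines then axitinib) and 10.5 + 4.8 = 15.3 months (sunitinib then axitinib). The article rounds these to medians of 26 and 15 months, and both sums reproduce. Visit times come from 2.3 and 2.9. The durations serve only to place the forms in time for a typical patient.

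**Forms expected under each section**

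| | Cytokines then axitinib | Sunitinib then axitinib |
|---|---|---|
| Second-line runs from / to (months) | 10.4 to 26.1 | 10.5 to 15.3 |
| Post-baseline forms, 2.3 | 3 (months 2, 4, end) | 3 (months 2, 4, end) |
| of these, in second-line | 1, at its end | 1, at its end |
| Post-baseline forms, 2.9 | 12 (months 2 to 24) | 7 (months 2 to 14) |
| of these, in second-line | 7 (months 12 to 24) | 2 (months 12, 14) |
| Gap from month 4 to the last form, 2.3 | 26.1 − 4 = 22.1 | 15.3 − 4 = 11.3 |

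**Share of the sequence after month 4 with no form until the end (2.3), at the rounded medians.** (26 − 4)/26 = 22/26 = 85%, and (15 − 4)/15 = 11/15 = 73%.

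**Timing of the last form.** 26 − 15 = 11 months later in the cytokine arm. The Discussion quotes 12 months for axitinib after cytokines, where 2.13 uses 15.7. With 12 months the cytokine sequence ends at 10.4 + 12 = 22.4 months, the gap from month 4 is 18.4 months, and the last form is 22.4 − 15.3 = 7.1 months later than in the sunitinib arm. The imbalance shrinks but remains.

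**How many patients could have a month-2 or month-4 form in second-line?** Assume exponential first-line durations with median m. The proportion off first-line by month t is 1 − 2^(−t/m).

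- Month 2: 12.5% (m = 10.4), 12.4% (m = 10.5).
- Month 4: 23.4% (m = 10.4), 23.2% (m = 10.5).

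About 77% are therefore still on first-line at month 4. For them the end form is the only one scheduled in second-line. For the other 23% or so, an early form may fall on axitinib if they have started it, but it is timed from first-line and is not a second-line baseline.

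**Who has no late form.** Under 2.3, patients who die on treatment or never start second-line have no form after month 4 that could be completed.

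**The case against.** The case for leaving the text alone has several parts.

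- **2.3 is the specific HRQOL text and would ordinarily govern.** In 2.9 the word examination is used mainly for physical and laboratory work, and the questionnaires are a separate list item. Fig. 3 and the full protocol are not shown and may resolve the point. This stands as a reason for caution about which schedule was run. It does not remove the inconsistency in the text, and if 2.3 prevails, the schedule with the weaker second-line data is in force.
- **A reader might infer that the two sections cannot both be followed.** The documents do not support that. The 2-monthly grid contains months 2 and 4, so the grid plus a form at the end of second-line satisfies both sections. The schedule is unclear, not impossible.
- **A reader might infer that endpoint 7 cannot be answered for second-line.** That goes too far. Change from pre-treatment baseline to the end of second-line can be computed and fits the wording of 2.14, although it mixes the effects of both lines. Under the 2.9 grid, second-line HRQOL would be measured repeatedly.
- **2.14 does not say that the HRQOL comparison is between arms**, whereas its sentence on adverse events does. The confounding argument therefore applies to any between-arm use of the last form, not to a test the plan has declared.
- **A reader might also infer that the month-4 form favours sunitinib**, because "one course consists of 4 weeks of administration and 2 weeks of withdrawal" and month 4 can land in the withdrawal weeks. This is too fragile to rely on. With 30.4-day months, month 4 (day 122) is cycle day 39 of 42, but month 2 (day 61) is cycle day 20 of 42, which is on drug. With 28-day months, month 4 (day 112) is cycle day 8 of 21 on the permitted alternative schedule, again on drug. Interruptions would shift the alignment further.

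**Conclusion.** The point holds in a limited form. Sections 2.3 and 2.9 are inconsistent on HRQOL timing and should be reconciled. If 2.3 governs, second-line HRQOL depends mainly on one event-triggered form, with no value at the start of axitinib and none scheduled during it. Change during second-line then cannot be estimated for most patients (about 77%, assuming exponential first-line durations with the planning medians). The last form falls about 11 months later in the cytokine arm at the planning medians, or about 7 months with the shorter axitinib figure from the Discussion. Secondary endpoint 7 is poorly supported for second-line, though not empty.

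The conclusion rests on reading the 2.9 grid as covering the questionnaires listed there, and on the planning durations as a rough guide to when forms fall. The primary endpoint and the sample size are unaffected.

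**What to change.** 1. Make 2.3 and 2.9 agree: give the three questionnaires at the existing 2-monthly and 3-monthly visits, and add one at the start of second-line.
2. In 2.14, base any between-arm HRQOL comparison on scheduled times from the start of treatment. Report the end-of-second-line form descriptively.
3. If only the 2.3 schedule was run, limit the between-arm HRQOL conclusion to the first 4 months and state that change during second-line was not measured.

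**Cost.** More questionnaires at visits that already take place, one form at the switch to axitinib, and some missing forms to handle. Enrolment closed in September 2017 and completion is planned for September 2020, so for visits already past only the wording of the endpoint and analysis can change. That can still be done before the final report.

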### Eligibility criteria: inclusion criteria

2.4

Patients are eligible to participate in the study if they:1.Have nephrectomy with mRCC;2.Have clear cell RCC diagnosis confirmed;3.Have had no prior systemic treatment for mRCC;4.Have MSKCC risk criteria of favorable or intermediate;5.Have at least one measurable lesion on computed tomography (CT) or magnetic resonance imaging (MRI) at the baseline per the Response Evaluation Criteria in Solid Tumors (RECIST) 1.1 criteria;6.Are aged 20–80 years;7.Have Eastern Cooperative Oncology Group (ECOG) performance status of 0 or 1;8.Have acceptable hematopoietic function defined as neutrophil ≥1,500/mm^3^, platelet ≥10 times 10^4^/mm^3^, hemoglobin >9.0 g/dL;9.Have acceptable hepatic function defined as total bilirubin ≤1.5 times ULN, AST and ALT ≤2.5 times ULN (patients with hepatic metastasis ≤5.0 times ULN);10.Have acceptable renal function defined as serum creatinine ≤2.0 times ULN;11.Have a life expectancy of more than 3 months; and12.Have provided informed consent for participation in the study after they received explanation of the briefing document.

### Ineligibility criteria: exclusion criteria

2.5

Patients are ineligible to participate in the study if they:1.Have a history of hypersensitivity against IFNα, IL-2, sunitinib, or axitinib;2.Are currently pregnant or suspected to be pregnant or are nursing, or plan to have a baby (including men);3.Have a history of hypersensitivity to biological preparations such as vaccines;4.Use Shou-Sai-Kotou (special herbal drug);5.Have autoimmune hepatitis;6.Have a history of interstitial pneumonia;7.Have been treated for another primary malignancy within 3 years of enrollment; and8.Fulfill investigator judgment of ineligibility.

### Informed consent: ethics approval

2.6

This study was conducted in accordance with the Declaration of Helsinki revised in 2008 and Ethical Guidelines for Clinical Research revised in 2008. All the treatment and examinations for mRCC are provided after written informed consent is provided. The institutional ethics committees of the participating institutions approved the ESCAPE study for mRCC.

### Methods of recruitment and random allocation

2.7

Recruitment was from October 2013 to September 2017. Eligible patients were randomly assigned to one of two treatment groups through the data center at the Innovative Clinical Research Center Kanazawa University (iCREK). Randomization was centrally performed by Waritsukekun (Mebix, Tokyo, Japan) using stratified sampling method to obtain adequate between-group balance for age (<70 or ≥ 70), MSKCC risk (favorable or intermediate), status of metastasis (lung only or other than lung), and participating institution.

### Administration of IFNα plus IL-2 vs. first-line therapy with sunitinib followed by second-line with axitinib

2.8

Patients assigned to cytokine group receive intravenous injection of IL-2 at a dose of 700,000 unit/day five days/week for the initial 2 or 4 weeks, and then, one or three times/week as maintenance plus subcutaneous injection of IFNα 5–6 million units two or three times/week (Fig. 2). Sunitinib at a dose of 50 mg/day is orally administered to patients who are assigned to the sunitinib group, and one course consists of 4 weeks of administration and 2 weeks of withdrawal. A schedule of 2 weeks of administration and one week of withdrawal is also permitted. Reduction of doses is permitted if a clinical investigator considers the basic doses inappropriate for any reason. The administration of IL-2 plus IFNα or sunitinib is terminated when progressive disease (PD) is confirmed based on RECIST v.1.1, the patient dies, or severe AEs occur. A clinical investigator administers axitinib as second-line treatment immediately after confirmed comprehensive evaluation of PD based on RECIST v.1.1 during first-line treatment. In case of cessation of first-line treatment because of severe AEs, a clinical investigator may consider restarting first-line treatment after recovery below grade 2. Axitinib at a dose of 10 mg/day (5 mg dose twice per day) is orally administered to patients as second-line treatment. Dose reduction or dose increase up to 20 mg/day (10 mg dose twice per day) is permitted if a clinical investigator considers the basic doses inappropriate for any reason. The administration of axitinib is terminated when PD is confirmed by comprehensive evaluation based on RECIST v.1.1, the patient dies, or severe AEs corresponding to discontinuation criteria occur. Zoledronic acid and denosumab are permitted for patients with bone metastasis.

